#### Criterion validity

The degree to which the results on the IOI-S are able to predict an outcome on established measures of eating disorder symptomatology (concurrent validity) [63] will be assessed as concordance between the IOI-S, the EDE-Q, and the SCOFF using a Spearman’s product moment correlation. Following, an Area Under Curve (AUC) analysis of Receiver Operating Characteristic (ROC) curve will be performed as analysis of IOI-S sensitivity and specificity threshold where a high sensitivity indicates accurate identification of true positive cases and high specificity indicates accurate identification of true negative cases [64]. Area Under Curve dictates the probability of identifying true positives or negatives by chance, where a value of 0.50 would suggest the measure is no more effective than guessing [65]. AUC threshold will be set at > 0.70 with a 95% confidence interval.

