## Methods/design

### Participants

Approximately 250 participants will be recruited into the study. They will be aged 14 and over, of all genders, and divided into two groups – clinical and non-clinical. Clinical status will be determined post-testing using EDE-Q cut-off scores. We aim to recruit across all DSM 5 diagnostic categories for eating disorders.

Participants will be recruited in two ways:
*Amazon’s Mechanical Turk (MTurk):* ‘MTurk’ is a global internet crowdsourcing service used frequently in academic research to recruit a broad base of willing research participants who are compensated for completing surveys, questionnaires and tasks as assigned by the researcher [45]. MTurk does not permit people under 18 to use its service: thus, it will be used to recruit adults aged 18+ only, both clinical and non-clinical. Participants will be able to sign up from anywhere in the world, deeming it an international cohort. They will be reimbursed according to MTurk recommendations.*Community:* Participants will be recruited via online advertisements on health websites and social media channels/paper advertisements. Advertisements will be aimed at individuals who self-report an eating disorder diagnosis, though those without an eating disorder are also welcome to participate, and all will go into the draw to win a Westfield gift card. We are specifically looking to recruit adolescents via this method, due to MTurk’s restriction on underage participants, however adults will also be targeted.

The use of two methods of recruitment aims to increase generalisability across age, ethnicity, gender and Body Mass Index (all of which will be reported) – this is significant due to the broad-reaching nature of the internet and the importance of validating the questionnaire across populations.

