### Baseline package

#### InsideOut institute screener (IOI-S) (InsideOut Institute for Eating Disorders, [44])

The six items of the new scale are displayed in Table 1. Item development followed review of the scientific literature for existing instruments screening and assessing eating disorder symptomatology, lived experience and clinical and research expert consultation. Instruments reviewed included the EDE-Q, the Eating Disorders Inventory (Garner et al., [46]), the SCOFF questionnaire, the ESP, and the Eating Attitudes Test (EAT; Garner et al., [47]), from which researchers developed an initial pool of 10 questions covering six facets of eating pathology: an individual’s relationship with food, body, the extent to which body weight and shape determines self-worth, loss of control over eating, binge eating and compensatory behaviour. This was further narrowed by an expert consultation team to six relevant items to evaluate eating pathology and eating disorder risk in a non-clinical population. The IOI-S is rated on a 5-point Likert scale, where 1 is “never” and 5 is “all the time”; except for Question 1, where 1 is “worry and stress free” and 5 is “full of worry and stress”. Responses are summed to yield a score between 6 and 30 points total, where 6 points is the lowest degree of risk and 30 points the highest degree of risk. Those deemed to be of moderate to high risk are directed to InsideOut’s database of trained professionals with expertise in eating disorders.

**Table 1 Tab1:** 6-item insideout institute screener

Item	1	2	3	4	5
1. How is your relationship with food?	Worry and stress-free	A bit problematic	Moderately problematic	Very problematic	Full of worry and stress
2. Does your weight, body or shape make you feel bad about yourself?	Never	A little bit	Sometimes	Quite a bit	All the time
3. Do you feel like food, weight or your body shape dominates your life?	Never	A little bit	Sometimes	Quite a bit	All the time
4. Do you feel anxious or distressed when you are not in control of your food?	Never	A little bit	Sometimes	Quite a bit	All the time
5. Do you ever feel like you will not be able to stop eating or have lost control around food?	Never	A little bit	Sometimes	Quite a bit	All the time
6. When you think you have eaten too much, do you do anything to make up for it?	Never	A little bit	Sometimes	Quite a bit	All the time

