### Sample size calculation

Estimated sample size is based on 2.5–3 times the minimum sample size required for power as the outcome measure (statistical validity) is incrementally increased with participant numbers. Therefore, we anticipate a total sample size of approximately 250 participants.

Approximately 30% of participants in each of the clinical and non-clinical groups (defined post T1 on EDE-Q cut-off score) will need to engage in the second task for sufficient validity. Estimated minimum sample size is based on the following analysis: in each group 10 participants are required for a power of 0.80 to detect an intraclass correlation coefficient of 0.70; 80 participants are required for sufficient power to detect a Spearman’s correlation of 0.40 or higher; 80 participants are required for good power to detect an Area Under Curve of 0.70, and at least 50 participants for a correlation coefficient of r +/− 0.70 for convergent and discriminant validity. All power analyses were conducted using PASS version 15 software [57].

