## Discussion

The internet is changing the way we seek and deliver healthcare, and current circumstances brought on by the COVID-19 global pandemic have intensified the need for validated online interventions and services, particularly where appropriate intervention at first point of contact is shown to be of fundamental gain to outcome. The primary outcome of this study is to establish if the Inside Out Institute Screener is a statistically reliable, valid and accurate online measure of eating disorder risk and symptomatology in those aged 14 and over so that it can be reliably used by those seeking information for a suspected eating disorder. The development of the tool was predicated on the understanding people now pursue support and information for healthcare concerns on the internet before presenting anywhere else, and the opportunity this presents to inform and encourage help-seeking behaviour in a population largely going undetected in primary healthcare [18]. Although primarily intended for personal use and potential self-referral, the screener is further designed to accurately identify clinical status and thus has the potential to be used in a clinical setting to distinguish true cases from non-cases, with treatment elucidated on that basis.

Questionnaires used in the field of eating disorders have mostly not been validated for online use. Instead, scores on each measure and respective community/clinical norms are derived from paper administration. This is often performed in conjunction with a trained clinician, which as stated, can confound results due to the nature of these types of questions being prone to denial and distortion on face-to-face assessment. Thus, lack of available norms for online administration may impact the findings. However, inclusion of the current gold-standard screening tools against which to validate was determined to be of necessary importance. Additionally, as all surveys are being delivered online in this instance, any effect due to test condition will be homogenous across the survey sample.

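### No numeric IOI-S cut-off is fixed before the single ROC analysis; a cut-off taken from that curve would have modestly overstated sensitivity and specificity

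*Protocol article*

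**What the plan says.** The Abstract (Methods) lists sensitivity and specificity among the four validity parameters to be reported for the IOI-S. Under Criterion validity, the AUC/ROC analysis is to be performed as "analysis of IOI-S sensitivity and specificity threshold", and the only numeric criterion is "AUC threshold will be set at > 0.70 with a 95% confidence interval".

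On the scale, the IOI-S section says "Responses are summed to yield a score between 6 and 30 points total". It adds "Those deemed to be of moderate to high risk are directed to" a professional database, without giving the scores that define those risk levels.

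On the sample, Participants says "Approximately 250 participants will be recruited into the study" and "Clinical status will be determined post-testing using EDE-Q cut-off scores". The Follow-up package collects the IOI-S alone. Sample size calculation sizes the ROC work only for the AUC: "80 participants are required for good power to detect an Area Under Curve of 0.70".

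On use, the Discussion sees potential for the screener in a clinical setting to "distinguish true cases from non-cases, with treatment elucidated on that basis".

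**The concern.** Sensitivity and specificity of a 6 to 30 sum score exist only at a cut-off. The article commits to reporting both, links the threshold to the ROC analysis and prints no cut-off beforehand. The natural reading is that the threshold comes from the curve. There is one sample with the EDE-Q, and the re-test has no EDE-Q, so no second sample is described in which a chosen cut-off could be checked.

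A cut-off selected because it performs best in a sample benefits from chance features of that sample. On average its accuracy there exceeds its accuracy in new people. The AUC interval shows neither this nor how uncertain the cut-off is, because the AUC summarises all cut-offs.

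At stake is how well users and clinics can rely on the stated accuracy. The Background treats false negatives as the costly error when it discusses the SCOFF threshold. With fewer cases than non-cases, most of the overstatement falls on sensitivity.

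**Working it through.** **1. The plan's own ROC figure.** The article gives 80 participants for an AUC of 0.70. It does not state the null value, alpha or numeric power, or clearly whether 80 is a total or per group. I assume null 0.50, two-sided alpha 0.05 and the Hanley-McNeil variance

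Var(A) = [A(1−A) + (n1−1)(Q1−A²) + (n0−1)(Q2−A²)] / (n1·n0), with Q1 = A/(2−A) and Q2 = 2A²/(1+A).

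For 40 cases and 40 non-cases:
- A = 0.70: Q1 = 0.5385, Q2 = 0.5765. Var = (0.21 + 39×0.0485 + 39×0.0865)/1600 = 0.00342, so SE = 0.0585.
- A = 0.50: Q1 = Q2 = 0.3333. Var = (0.25 + 78×0.0833)/1600 = 0.00422, so SE = 0.0650.
- Power = Φ[(0.20 − 1.96×0.0650)/0.0585] = Φ(1.24) = 0.893.

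With 80 per group, power is 0.996. So 80 in total is compatible with good power if the groups are equal, but the match cannot be confirmed. Either way the figure concerns the AUC and says nothing about accuracy at a cut-off.

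**2. Inputs for the cut-off check.**
- From the article: N = 250, integer scores 6 to 30, hence 24 possible rules (positive if score ≥ 7, …, ≥ 30).
- Assumed: cases 50% or 20%, since EDE-Q groups are formed after testing; true AUC 0.70, 0.80 or 0.90; normal scores with equal SD 5 and non-case mean 14, rounded and clipped to 6–30; case mean = 14 + 5·√2·Φ⁻¹(AUC); cut-off chosen by the largest sensitivity + specificity − 1 (Youden).

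**3. Method.** In each of 3,000 simulated studies, select the cut-off, then take

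optimism = apparent value at the chosen cut-off − true value at the same cut-off,

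and average, separately for sensitivity and specificity.

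**4. Results (percentage points).**

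| Cases / non-cases | AUC | Sensitivity | Specificity | Sum | Chosen cut-off, 5th–95th percentile |
|---|---|---|---|---|---|
| 125 / 125 | 0.70 | 1.9 | 1.9 | 3.9 | 14–19 |
| 125 / 125 | 0.80 | 1.4 | 1.6 | 3.0 | 15–19 |
| 125 / 125 | 0.90 | 1.3 | 1.3 | 2.6 | 17–21 |
| 50 / 200 | 0.70 | 4.5 | 1.0 | 5.5 | 13–20 |
| 50 / 200 | 0.80 | 3.5 | 0.8 | 4.3 | 15–20 |
| 50 / 200 | 0.90 | 2.7 | 0.6 | 3.4 | 17–21 |

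(Sums were computed before rounding.)

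**5. Stability of the check.** A repeat with 10,000 simulated studies gave sensitivity/specificity optimism of 1.9/2.0 and 1.2/1.3 for 125/125, and 4.2/1.1 and 2.7/0.7 for 50/200 (AUC 0.70 and 0.90). The range 13–20 became 13–19. With SD 4 the optimism hardly changed, but the cut-off ranges narrowed to 2 to 4 points. The width of the cut-off range therefore depends on the assumed spread of scores, and about 3 to 6 points is a fair summary.

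**6. Scale against sampling error.** At a sensitivity of 0.80, the 95% half-width is 1.96×√(0.8×0.2/n): 7 points for 125 cases and 11 points for 50. The mean optimism lies well inside this. Unlike sampling error, however, it always pushes in the favourable direction, and an ordinary interval around the apparent value does not remove it.

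**The case against.** The strongest case against is that the article states no selection procedure. It names no best point, and its one numeric criterion, the AUC, involves no cut-off. A reader might infer that the plan commits to publishing uncorrected accuracy at an optimised cut-off. The text does not say so: a selection rule and internal validation may sit in a full protocol or analysis plan that is not shown, and silence in a condensed article does not exclude them.

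The tool may also already have numeric risk bands, since users at moderate to high risk are referred. Accuracy evaluated at an existing band would carry no selection optimism.

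The upper figures also rest on AUC 0.70. The article seeks a correlation above 0.70 with the EDE-Q, which also defines the cases. Under bivariate normality a correlation of 0.70 implies an AUC of about 0.83 to 0.87 for 50% to 10% cases. At AUC 0.85 the optimism is 1.4/1.4 points (sensitivity/specificity) with 125/125 and 3.1/0.8 with 50/200. Finally, the Discussion puts personal use and self-referral first and treats clinical use as a potential.

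Most of this stands, and it makes the point conditional and its size modest. It does not remove the point. The article promises sensitivity and specificity, places the threshold in the ROC analysis, gives no numbers for the risk bands, and describes one sample with the reference standard. Followed as written, that yields apparent accuracy at a data-derived cut-off.

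**Conclusion.** The point holds conditionally, with moderate confidence. The Criterion validity section ties the threshold to one ROC analysis in the only sample with the EDE-Q, fixes no numeric cut-off, and guards the result only with a threshold-free statistic. If the cut-off is read off that curve, its stated accuracy will be modestly too high: about 1 to 2 points for each measure with balanced groups, and about 3 to 4.5 points of sensitivity and 1 point of specificity with 20% cases, for AUC 0.90 to 0.70. The cut-off would vary by about 3 to 6 score points between equally valid samples, which is arguably the larger practical matter.

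These sizes assume the Youden rule, equal-variance normal scores, N = 250 and the two case splits; another rule would give other figures. A reader might go further and conclude that the AUC result is biased too. It is not: the AUC of a fixed sum score involves no selection of a cut-off, so the AUC > 0.70 criterion stands as planned.

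**What to change.** In Criterion validity, choose one of two routes and say which.

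- **Existing cut-off:** if the risk bands already have numeric limits, state them before the data are analysed and report sensitivity and specificity there, with ordinary confidence intervals.
- **Cut-off from the ROC curve:** name the selection rule and repeat the whole selection in at least 1,000 bootstrap resamples. For each resample, take accuracy at its own cut-off in the resample minus accuracy at that same cut-off in the full sample. Subtract the average difference from the apparent values. Report the corrected sensitivity and specificity, with the bootstrap interval of the cut-off itself.

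If the full protocol or analysis plan already contains one of these, a sentence saying so is enough.

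The cost is a few lines of code and slightly less favourable stated accuracy. No extra participants or data are needed.

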#### Construct validity

Convergent validity, or the degree to which the IOI-S correlates with eating disorder constructs and variables on both the EDE-Q and the SCOFF [66] will be measured with a correlation coefficient threshold set at *r >* 0.70. A correlation coefficient will also be determined for discriminant validity between the IOI-S and MC-SDS/CSD-S. A correlation coefficient of +/− 0.70 indicates a strong linear relationship between two variables [67].

#### Missing and outlier values

REDCap online survey platform can be configured to eliminate missing values, otherwise submission of the survey battery is not possible. If data is not normally distributed, Spearman’s Rank Order will be used instead of Pearson’s correlation coefficient.

## Discussion

The internet is changing the way we seek and deliver healthcare, and current circumstances brought on by the COVID-19 global pandemic have intensified the need for validated online interventions and services, particularly where appropriate intervention at first point of contact is shown to be of fundamental gain to outcome. The primary outcome of this study is to establish if the Inside Out Institute Screener is a statistically reliable, valid and accurate online measure of eating disorder risk and symptomatology in those aged 14 and over so that it can be reliably used by those seeking information for a suspected eating disorder. The development of the tool was predicated on the understanding people now pursue support and information for healthcare concerns on the internet before presenting anywhere else, and the opportunity this presents to inform and encourage help-seeking behaviour in a population largely going undetected in primary healthcare [18]. Although primarily intended for personal use and potential self-referral, the screener is further designed to accurately identify clinical status and thus has the potential to be used in a clinical setting to distinguish true cases from non-cases, with treatment elucidated on that basis.

Questionnaires used in the field of eating disorders have mostly not been validated for online use. Instead, scores on each measure and respective community/clinical norms are derived from paper administration. This is often performed in conjunction with a trained clinician, which as stated, can confound results due to the nature of these types of questions being prone to denial and distortion on face-to-face assessment. Thus, lack of available norms for online administration may impact the findings. However, inclusion of the current gold-standard screening tools against which to validate was determined to be of necessary importance. Additionally, as all surveys are being delivered online in this instance, any effect due to test condition will be homogenous across the survey sample.

This study aims to recruit a large pool of applicants of diverse ethnicity, age, clinical presentation and gender. This is achieved by the use of two recruitment arms – one of which, MTurk, has a broad global reach – and will greatly increase generalisability. It will be one of the first to assess and identify risk on a spectrum rather than classifying true cases and non-cases only, with the aim of improving early intervention in subsyndromal presentations.

The study’s significance will lie in its contribution to e-health early intervention and general screening efficacy across a spectrum of eating disorders. Given the prognostic implications of early intervention and current circumstances surrounding COVID-19, the importance of building e-health resources for an adaptable health system intended to encourage help-seeking cannot be underestimated.

## Data Availability

Not applicable.

## Abbreviations

AN: Anorexia Nervosa
ARFID: Avoidant Restrictive Food Intake Disorder
BED: Binge Eating Disorder
BN: Bulimia Nervosa
EAT: Eating Attitudes Test
ED: Eating Disorder
EDE-Q: Eating Disorder Examination Questionnaire
EDE-QS: Eating Disorder Examination Questionnaire Short
EDI: Eating Disorders Inventory
IOI-S: InsideOut Institute Screener
OSFED: Other Specified Feeding or Eating Disorder
SCOFF: Sick, Control, One Stone, Fat Food questionnaire
MC-SDS: Marlowe-Crowne Social Desirability Scale
CSD-S: Children’s Social Desirability Short Scale
